# Effectiveness and implementation success of a co-produced physical activity referral scheme in Germany: study protocol of a pragmatic cluster randomised trial

**DOI:** 10.1186/s12889-022-13833-2

**Published:** 2022-08-13

**Keywords:** Physical activity, Physician-initiated PA promotion, Physical activity-related health competence, Cluster design, Pragmatic trial

## Abstract

**Background:**

While effective physical activity referral schemes (PARSs) and related structures for promoting physical activity (PA) already exist in several countries, in Germany, PARSs have not yet been implemented systematically and nationwide. Through a co-production approach with relevant actors in the German healthcare system, a PARS was developed, and an implementation plan was created (e.g. financing). This study protocol aims to evaluate the developed PARS for people with non-communicable diseases (NCDs) in Germany regarding its potential effectiveness and implementation success.

**Methods:**

To evaluate the effectiveness and implementation success of the PARS, we will apply a pragmatic cluster-randomised controlled trial (cRCT) in Hybrid II design by comparing two intervention groups (PARS vs PA advice [PAA]). The trial will take place in the Nürnberg metropolitan region, with 24 physician practices recruiting 567 people with NCDs. Both groups will receive brief PA advice from a physician to initially increase the participants’ motivation to change their activity level. Subsequently, the PARS group will be given individualised support from an exercise professional to increase their PA levels and be transferred to local exercise opportunities. In contrast, participants in the PAA group will receive only the brief PA advice as well as information and an overview of regional PA offerings to become more active at their own initiative. After 12 and 24 weeks, changes in moderate to vigorous PA and in physical activity-related health competence (movement competence, control competence, self-regulation competence) will be measured as primary outcomes. Secondary outcomes will include changes in quality of life. To measure implementation success, we refer to the RE-AIM framework and draw on patient documentation, interviews, focus groups and surveys of the participating actors (physicians, exercise professionals).

**Discussion:**

Through a between-group comparison, we will investigate whether additional individual support by an exercise professional compared to brief PA advice alone leads to higher PA levels in people with NCDs. The acceptance and feasibility of both interventions in routine care in the German healthcare system will also be evaluated.

**Trial registration:**

ClinicalTrials.gov, NCT04947787. Registered 01 June 2021.

**Supplementary Information:**

The online version contains supplementary material available at 10.1186/s12889-022-13833-2.

## Background

In Germany, only approximately 45% of adults are adequately physically active and meet the national and international physical activity (PA) recommendations of at least 150 min/week of moderate to vigorous activity or 75 min/week of intensive activity [1]. The worldwide increase in physical inactivity has led not only to an increase in non-communicable diseases (NCDs) and mortality rates but also to rising medical costs [2]. Regular PA has been associated with comprehensive positive physical and mental health effects, as scientifically demonstrated for more than 25 NCDs, including obesity, type 2 diabetes mellitus and cardiovascular diseases [3]. Despite these benefits, persons with chronic diseases in particular show considerably lower PA levels compared to healthy adults [4].

Physicians have been prescribing PA for over 2,500 years. The Indian physician Susruta, for example, recommended PA for his patients as early as 600 BC, and Hippocrates (460 – 370 BC) wrote the first-known exercise prescription for patients to manage chronic diseases [5]. Today, physician-initiated exercise is recommended in the European Union (EU) PA Strategy, the Global Action Plan on Physical Activity 2018–2030 (WHO) and German guidelines for PA and PA promotion (NEBB) as an effective PA measure [6, 7]. Accordingly, there are already established structures for physician-initiated PA promotion, such as ‘Exercise on referral’ (England) [8], ‘Physical activity on prescription’ (Sweden) [9] and ‘Green prescription’ (New Zealand) [10]. In Germany, physicians already make PA recommendations as part of routine care but without referring to an existing PA service or receiving financial compensation for the services provided [11].

The project *BewegtVersorgt*, funded by the German Federal Ministry of Health, aims to develop structures to promote PA for people with NCDs and to equip individuals with the competences necessary to lead a healthy, physically active lifestyle [12]. Based on a co-production process with relevant actors in the German healthcare system, a physical activity referral scheme (PARS) was developed, as detailed in Weissenfels et al. [13]. Following other promising referral schemes, key constituent elements, such as PA screening, assessment, counselling, referral form/prescription, feedback and follow-up [14], were identified and adapted to the structures of the German healthcare system. International studies have shown that these referral schemes have a meaningful impact, but the results vary widely, and merely transferring a specific concept to other healthcare systems is typically not feasible [15, 16].

Internationally, there are also simpler healthcare structures than PARS for PA promotion, such as PA advice (PAA), that provide good evidence for individuals’ initial motivation to change their PA behaviour but remain questionable regarding long-term PA promotion [17]. Therefore, the current study aims to compare a PARS and PAA intervention group to examine whether the individual support of an exercise professional using behaviour change techniques in the PARS group produces a more significant change in PA behaviour than in the PAA group.

### Objectives

Based on a Hybrid II design [18], the objectives of the pragmatic trial are twofold. The first objective is to evaluate the effectiveness of the developed PA interventions (PARS vs PAA) in terms of a) increasing moderate to vigorous PA, b) changes in physical activity-related health competence (PAHCO) (movement competence, control competence, self-regulation competence, see Carl et al. [19, 20]) and c) influencing the quality of life of people with NCDs. The second objective is (d) to test the success of the implementation plan. The following study protocol focuses particularly on evaluating effectiveness as more details on the success of the implementation plan will be presented in another article.

#### Primary hypotheses

The key elements of the PA interventions focus on the improvement of PAHCO and long-term changes in PA levels, so both outcomes are considered equally important as primary endpoints.

The PARS group members increases their (subjective) PA significantly after 12 and 24 weeks compared to the PAA group.

2)The PARS group members report significant improvements in PAHCO after 12 and 24 weeks compared to the PAA group.

#### Secondary hypothesis

3)The PARS group shows a significant increase in quality of life after 12 and 24 weeks compared to the PAA group.

#### Further hypothesis

4)Participating actors (physicians, exercise professions) are able to implement the developed PA interventions in routine care and evaluate them positively. 

### Trial design

The study described in this protocol is a cluster-randomised controlled trial (cRCT) with two intervention arms (PARS vs PAA) and is designed to be pragmatic using the PRECIS-2 tool [21]. Based on the pragmatic application, the trial is guided by a Hybrid II design, following Curran et al. [18], which simultaneously tests the effectiveness of the interventions and the implementation plan. The study will be conducted as a pilot project in the Nürnberg metropolitan region, Germany, and will be scientifically supported by the Friedrich-Alexander-Universität Erlangen-Nürnberg (FAU), Germany.

This protocol is based on the Standard Protocol Items: Recommendations for Interventional Trials (SPIRIT) [22]. An overview of schedule of enrolment, both interventions, and assessments is provided in Fig. 1. The pragmatic trial will be conducted and reported in accordance with the reporting guidelines provided in the CONSORT 2010 statement [23], taking into account the CONSORT extension for pragmatic trials [24] and cRCTs [25].

**Fig. 1 Fig1:**
[figure not shown]
Schedule of enrolment, interventions, and assessments following SPIRIT. PA physical activity; PARS physical activity referral scheme; PAA physical activity advice; EQ-5D-5L European Quality of Life – 5 Dimensions – 5 Level; SSA self-efficacy towards physical activity; HCCQ-D Health Care Climate Questionnaire; SSK sport- and movement-related self-concordance; PREMs patient-reported outcome measures

## Methods

### Study setting and participants

The PARS was developed using a co-production approach that involved all relevant actors in the healthcare system (e.g. healthcare service providers, healthcare insurance providers, representatives of patient associations; *n* = 12 organisations). More information about the co-production process can be retrieved from the study protocol covering all project phases (development, implementation, evaluation, scaling-up) [13]. The pragmatic trial will take place in the German primary healthcare setting. As part of a routine examination, suitable patients will be recruited by physicians (general practitioners and medical specialists) and screened for eligibility. Participants are eligible for the study if they (a) are at least 18 years old and live in the Nürnberg metropolitan region; (b) have at least one of the following NCDs: controlled diabetes mellitus type 2, chronic cardiovascular disease, obesity (Body Mass Index [BMI] ≥ 30 kg/m^2^) or arthrosis in knee and/or hip; (c) do not meet official German PA recommendations (i.e. performing less than 150 min of moderate to vigorous aerobic activity per week); (d) are insured with health insurance companies cooperating with the project and (e) can safely participate in PAs based on medical judgement. Individuals will be excluded if they (a) plan to leave the Nürnberg metropolitan region during the study period, (b) are participating in another study, (c) plan to be absent for more than four weeks during the 12-week intervention, (d) have cognitive impairments that prevent an effective communication with the physician and the exercise professional, (e) have a mental illness, such as psychosis, substance abuse or mood and personality disorders, (f) have an unstable clinical situation or serious health impairments that prevent them from undertaking PA safely (e.g. acute myocardial infarction, unstable angina pectoris, fever, terminal tumour diseases).

### Recruitment procedures

#### Physicians

The recruitment of participants will take place via trained physicians in the Nürnberg metropolitan region. Participating general practitioners and medical specialists will be recruited through ‘quality circles’ (a continuing education programme for physicians), medical associations, a regional Bavarian science journal and the homepages of the project stakeholders. The project stakeholders consist of 12 organisations from the German healthcare system and include representatives from patients, the medical profession, the exercise professions, and insurance providers.

Inclusion criteria will be that the physicians (a) are located in the Nürnberg metropolitan region, (b) work in general medicine or specialise in internal medicine (cardiology, diabetology or endocrinology), orthopaedics, physical and rehabilitative medicine or geriatrics, (c) have expressed their willingness and commitment to participate in the study, (d) have adequate resources to manage the study and comply with the protocol, (e) have adequate patient volume according to participants’ inclusion criteria (given diseases, healthcare insurance) and (f) participate in a 90-min digital training session (introduction to motivational interviewing and interview guide for PA advice). Exclusion criteria will be (a) participation in conflicting studies and (b) practice relocation or retirement planned during the study period.

#### Participants

Suitable patients from the cooperating health insurance companies will be included in the study as part of their routine care (pragmatic trial). Eligible patients will be identified by the physicians or medical staff in advance (see inclusion and exclusion criteria above). Selected patients will receive information about the study and a screening assessment at their routine appointment (see Fig. 2), which will ask about their PA levels and contraindications. After a brief conversation about the benefits of PA with the physician, the patient can decide whether to participate in the programme and is referred to the next level of each intervention arm.

**Fig. 2 Fig2:**
[figure not shown]
Study design with both groups (PARS vs PAA)

#### Exercise professionals (PARS group only)

Exercise professionals (e.g. physiotherapists, sport and exercise therapists) will be recruited using various strategies. An overview of all facilities related to PA promotion (physiotherapy practices, rehabilitation sports, prevention sports and fitness facilities related to health promotion) in the Nürnberg metropolitan region has already been compiled. The study team will systematically contact the responsible staff of each facility via telephone to present the study as well as general conditions and ascertain levels of interest. If the facility staff express interest, the responsible exercise professionals will participate in a 1.5-day digital training course in which they are familiarised with the intervention (individual PA promotion and assessments) and will have the opportunity to try out motivational interviewing. The study team will also advertise the project through project stakeholders’ websites, newsletters and information letters to the stakeholders’ members.

### Sample size

To calculate the number of participants, we focus on the primary endpoints of ‘moderate to vigorous PA (min/week)’ and ‘PAHCO’, including cluster adjustment. As the primary outcomes lead to four statistical tests, a Bonferroni correction is used accordingly with *α *= 0.05/4. With an assumed drop-out rate of 10%, a sample size of 567 participants from 24 medical practices (α = 0.0125, power = 80%) is required to detect differences between both intervention groups of low to moderate effect size (*f* = 0.175). To account for the effects of clustering, an intraclass correlation (ICC) of 0.02 is considered, estimated based on previous studies for cRCTs in primary care [26, 27]. We consider this ICC to be realistic in our trial as the participating practices are similarly structured (professional background, qualification level, treating patient group size and region) and were trained by the research team.

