#### Physical activity (PA)-related health competence

Changes in PAHCO will be measured using the German version of the Physical Activity-Related Health Competence Questionnaire (BGK Questionnaire) [12, 37]. The questionnaire consists of 42 items that measure the following three sub-competencies necessary for health-promoting PA behaviour: movement competence (18 items; min = 0, max = 17.6), control competence (10 items; min = 0, max = 10.8) and self-regulation competence (14 items; min = 0, max = 14.8). Higher scores indicate higher competencies.

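### The Bonferroni divisor counts four primary tests, but the primary outcomes as written give eight comparisons, so 5% family-wise error is not guaranteed

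*Protocol article*

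**What the plan says.** The Sample size section of the protocol article names MVPA and PAHCO as the primary endpoints and continues: "As the primary outcomes lead to four statistical tests, a Bonferroni correction is used accordingly". Alpha becomes 0.05/4 = 0.0125. With 80% power, f = 0.175, ICC 0.02 and 10% drop-out, this leads to 567 participants in 24 practices. The four tests are not listed.

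Four other places bear on the count:

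- **Abstract, Methods.** For both follow-up visits, at week 12 and week 24, the text reads: "changes in moderate to vigorous PA and in physical activity-related health competence (movement competence, control competence, self-regulation competence) will be measured as primary outcomes". The Objectives section names the same three competences.
- **Outcome section on PAHCO.** "The questionnaire consists of 42 items that measure the following three sub-competencies necessary for health-promoting PA behaviour". Each has its own number of items (18, 10, 14) and its own maximum (17.6, 10.8, 14.8). No overall score is defined.
- **Primary hypotheses.** The PARS group "increases their (subjective) PA significantly after 12 and 24 weeks compared to the PAA group", and "The PARS group members report significant improvements in PAHCO after 12 and 24 weeks compared to the PAA group". The two endpoints are given equal rank, and neither time point is put ahead of the other.
- **Data analysis.** The group effect is modelled on outcomes after the intervention, adjusted for baseline. No joint test over visits or sub-competences and no testing order is stated.

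**The concern.** A Bonferroni correction protects the family-wise error only if the divisor is at least the number of tests that can each produce a claim. Four measures at two visits are eight comparisons, and the divisor is four.

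Two things are at stake. If each of the eight results may be called a significant primary result at 0.0125, the chance of at least one false claim can exceed 5%. If the divisor is raised to eight, the stated 80% power is no longer what 567 participants deliver under the plan's own assumptions. Because the four tests are not identified, the choice of which four count could also be made after the data are seen.

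**Working it through.** **Inputs.** From Sample size: f = 0.175, which is d = 2f = 0.35 for two equal groups; alpha 0.0125; power 80%; ICC 0.02; 24 practices; drop-out 10%; N = 567. Sidedness is not stated; two-sided testing reproduces N and is used throughout.

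**1. Reproducing the stated sample size.**
- Without clustering: N = 4 × (z(0.99375) + z(0.80))² / d² = 4 × (2.498 + 0.842)² / 0.1225 ≈ 364.1.
- With clustering, design effect 1 + (N/24 − 1) × 0.02, solved for N: 364.1 × 0.98 / (1 − 364.1 × 0.02/24) = 512.3 analysed.
- With drop-out: 512.3 / 0.90 = 569.2. The stated 567 is within 0.4%. An ANOVA F version gives 578, 1.9% away.

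So 567 follows correctly from alpha = 0.0125. Only the divisor is in question.

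**2. Counting the comparisons.** MVPA + 3 sub-competences = 4 measures; 4 measures × 2 visits = 8.

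**3. Family-wise error at 0.0125 per test.**
- Four independent tests: 1 − (1 − 0.0125)^4 = 4.9%, as intended.
- Eight tests, upper bound: 8 × 0.0125 = 10.0%.
- Eight independent tests: 1 − (1 − 0.0125)^8 = 9.6%.
- Eight correlated tests. The article gives no correlations, so a range is assumed (simulation of correlated normal statistics, 2,000,000 draws):

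| Common correlation | Family-wise error |
|---|---|
| 0.3 | 8.8% |
| 0.5 | 7.5% |
| 0.7 | 5.8% |
| 0.8 | 4.7% |

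Unequal patterns give similar values. With 0.5 between visits and 0.3 between measures the error is 8.7%; with 0.8 and 0.5 it is 6.9%.

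**4. Power at 567 enrolled.**
- Analysed: 567 × 0.90 = 510.3, or 510.3/24 = 21.26 per practice.
- Design effect: 1 + 20.26 × 0.02 = 1.405. Effective N: 510.3 / 1.405 = 363.1.
- Non-centrality: 0.35 × √(363.1/4) = 3.335.
- Alpha 0.0125: Φ(3.335 − 2.498) = 79.9%, which is the stated 80%.
- Alpha 0.05/8 = 0.00625: Φ(3.335 − 2.734) = 72.6%.

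**5. Sample size for 80% power at 0.00625.** 417.6 without clustering, 627.6 analysed, 627.6/0.90 ≈ 697 enrolled (F version about 709). That is about 23% above 567.

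**The case against.** The strongest reply is that four is a coherent count. Sample size names two endpoints, Primary hypotheses treats them as two, and each is stated at two visits: 2 × 2 = 4. On that reading, the competences in brackets in the Abstract only say what PAHCO covers. The outcome section describes sub-scales without saying that each is tested, and how they are combined may be set out in a full analysis plan that is not shown. The multilevel structural equation model offered as one option under Data analysis could carry PAHCO as one construct.

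Other routes also lead to four: a single joint test over both visits per measure, or a rule that a measure succeeds only if it is significant at both visits. Under that last rule each measure's error is at most 0.0125 and the family's at most 4 × 0.0125 = 5%.

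This stands in part. A reader might infer that eight tests is the only possible reading, or that 5% control definitely fails. The article does not support either, because it does not exclude these rules. But it does not state any of them, and the divisor is not a detail left for later: it is a fixed design figure that sets alpha and N.

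The reply is also right that repeated measurements and sub-scales of one questionnaire are probably positively correlated, so the inflation is likely to be below the 10% bound.

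On power, the planned baseline adjustment may recover the loss. If f = 0.175 is on the unadjusted scale (not stated) and the ICC is unchanged, a baseline-outcome correlation of 0.4 gives a non-centrality of 3.335/√(1 − 0.16) = 3.639 and power Φ(3.639 − 2.734) = 81.7–81.8% at 0.00625. That correlation is an assumption; the article gives none.

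**Conclusion.** The point holds in this form: the stated count of four does not match the primary outcomes as written, which give eight comparisons, so 5% family-wise control is not guaranteed. If all eight are tested at 0.0125, the error is at most 10%. It lies between 9.6% (independent) and 5.8% (common correlation 0.7), and drops below 5% only at a correlation of nearly 0.8 or more. Correcting the divisor instead costs about 7 percentage points of power, from 79.9% to 72.6%, before any gain from baseline adjustment.

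Two stronger readings should be avoided. Doubling of the error is the upper bound, not the expected size. And a power of 62.4%, which results from 0.00625 with a t reference on 22 degrees of freedom (24 practices less 2), should not be charged to the divisor: with 22 degrees of freedom the article's own 0.0125 already gives 72.5%. The degrees of freedom are a separate matter.

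**What to change.** Before analysis, state a confirmatory family of exactly four tests that matches the divisor. Any of these would do:

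- MVPA and the three sub-competences at one primary time point, with the other time point secondary;
- one test per measure that covers both visits, either joint or requiring significance at both;
- a single defined PAHCO score and PA, each at 12 and 24 weeks.

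The alpha of 0.05/4 and the 567 then stand. The choice among them is the investigators'; the article does not favour one time point over the other. If significance at both visits is required, the 80% applies to each visit, and the chance of success at both lies between 2 × 0.799 − 1 = 59.8% and 79.9% under the same assumptions. This should be said.

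Alternatively, keep all eight comparisons as primary, use 0.05/8 = 0.00625 and restate the power at 567 as about 73%. Holm's procedure is an optional refinement with the same error control and at least the power of single-step Bonferroni.

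The cost is wording: no new data and no change to conduct. The downside is that some comparisons become secondary, or that the stated power looks less favourable.

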### Randomisation, allocation and blinding

A cRCT with randomisation at the physician practice level will be conducted for organisational reasons and to avoid the risk of mixing participants from both groups within a medical facility (contamination). The research team will recruit the physicians and provide them with detailed information about the study or answer questions. After physicians express interest in participating in the study and meet the inclusion criteria, they must provide written informed consent, which needs to be supported by the cooperating health insurance company. Each medical practice will be randomly allocated to the PARS or PAA group using computer-based block randomisation (Excel 2016). Due to the local density of physician practices in the Nürnberg metropolitan region, six blocks for randomisation will be defined (Nürnberg city [*n* = 10], Nürnberg surrounding area [*n* = 2], Fürth city [*n* = 10], Fürth surrounding area [*n* = 2], Erlangen city [*n* = 10] and Erlangen surrounding area [*n* = 2]). The practices will then be informed about further procedures, and physicians, as well as medical staff working in the facility, will undergo specific training according to the assigned intervention arms.

Because of group-specific procedures and the corresponding training, blinding the participating actors (physicians, exercise professionals) is not possible in this study. However, blinding participants is possible due to randomisation on the physician practices’ level. The participants will only be informed about the intervention in which they are involved and will not come into contact with the other intervention arm during the study. The statistician will also be blinded to the group allocation until completion of the statistical analysis.

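### Holm's step-down procedure, in place of single-step Bonferroni for the primary tests, would recover power on every rejection after the first under the same 5% family-wise error limit

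*Protocol article*

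**What the plan says.** The multiplicity rule appears once, in the protocol article under Sample size: "As the primary outcomes lead to four statistical tests, a Bonferroni correction is used accordingly". The level per test is 0.05/4 = 0.0125, and the power is 80%. The same section gives the planning result, "With an assumed drop-out rate of 10%, a sample size of 567 participants from 24 medical practices", for an effect of f = 0.175, and adds that "an intraclass correlation (ICC) of 0.02 is considered".

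Under Primary hypotheses, PA and PAHCO are given the same rank: "both outcomes are considered equally important as primary endpoints". Both hypotheses are framed over 12 and 24 weeks. The Data analysis section describes the models and the handling of missing data but names no multiplicity procedure. The article gives no reason for single-step testing and plans no simultaneous confidence intervals.

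**The concern.** Single-step Bonferroni holds each test at 0.0125 whatever the other tests show. Holm's procedure orders the p-values and compares them in turn with 0.05/4, 0.05/3, 0.05/2 and 0.05, stopping at the first failure. It uses the same p-values, needs no pre-set order and no assumption about dependence, and keeps the family-wise error within 5%. Every Bonferroni rejection is also a Holm rejection. Because the endpoints are ranked equally, nothing in the design stands in the way of Holm.

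The difference lies only in rejections after the first. These matter here because the trial predicts benefit on both outcomes at both time points. Once one test has succeeded, Bonferroni still asks the remaining tests to meet the strictest threshold.

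**Working it through.** **Inputs from the protocol article (Sample size):** alpha 0.0125 per test, power 80%, f = 0.175, ICC 0.02, 24 practices, 10% dropout, N = 567.

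**Assumptions, not stated in the article:** two-sided tests, 1:1 allocation, and the correlation between the four test statistics, varied from 0 to 0.9.

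**Step 1: reproduce the planned figure.**
- For two groups, d = 2f = 0.35.
- The critical value is z(1 − 0.0125/2) = 2.498, and z(0.80) = 0.842.
- The normal approximation gives n per arm = 2(2.498 + 0.842)²/0.35², rounded up to 183, so 366 in total. The F-test version gives 368.
- The analysed cluster size is about 567 × 0.9/24 ≈ 21, so the design effect is 1 + (21 − 1) × 0.02 = 1.40.
- 368 × 1.40 × 1.10 = 567, the stated N. Dividing by 0.9 instead of multiplying by 1.10 gives about 573. Power at 567 is 79.9% (normal) or 79.5% (F).

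The planning figure is reproduced.

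**Step 2: compare the procedures.** Four two-sided z-tests were simulated, each real effect having mean 2.498 + 0.842 = 3.34 (80% power at 0.0125), with 1,000,000 replicates per scenario. Entries are Bonferroni → Holm.

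| Scenario | Correlation 0 | 0.5 | 0.9 |
|---|---|---|---|
| Four real: power per test | 80% → 89.5% | 80% → 87.5% | 80% → 85.1% |
| Four real: all four rejected | 41.1% → 69.1% | 55.6% → 75.9% | 70.2% → 82.7% |
| Four real: at least one rejected (both methods) | 99.8% | 96.7% | 88.5% |
| Two real: power per test | 80% → 82.3% | 80% → 82.0% | 80% → 81.5% |
| Two real: both rejected | 63.9% → 68.5% | 68.7% → 72.6% | 75.0% → 78.0% |

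With one real effect, power per test goes from 80.0% to 80.1% at most. With four real effects, Holm rejects at least one more hypothesis in 33% (correlation 0), 25% (0.5) or 14% (0.9) of trials. No Bonferroni rejection was lost in any replicate.

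**Step 3: family-wise error.** Under the global null at correlation 0.5 it is 4.3% for both methods. The largest value for Holm in any scenario was 4.95%.

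**Step 4: what the gain is worth in patients.** Take 87.4% power per test, for which z = 1.146. The effective sample must grow by (2.498 + 1.146)²/(2.498 + 0.842)² = 1.19, from 366 to about 436. With 24 practices fixed, N/[1 + (N/24 − 1) × 0.02] must equal the effective sample, so N = 0.98 × n_eff/(1 − 0.02 × n_eff/24).
- n_eff = 366: N = 358.7/0.695 = 516.
- n_eff = 435.7: N = 426.9/0.637 ≈ 670.
- Ratio: 670/516 ≈ 1.30.

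Matching that power with Bonferroni would take about 30% more analysed patients. The 19% applies only if practices are added in proportion.

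**The case against.** The strongest reply is that Bonferroni appears only in the sample-size section, where it sets the planning alpha. Sizing at 0.05/4 is compatible with Holm testing, and an analysis plan that is not shown might already name Holm. If so, the point falls away. As written, however, the sentence says that the correction is used because there are four tests, and nothing else in the article names a testing rule. The natural reading is that it governs the tests too.

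The second reply is that nothing is invalid. That stands: Bonferroni controls the error and the trial has the power per test that it planned. A reader might infer that the trial is underpowered or its multiplicity control faulty. The documents do not support this, since the stated N and power are reproduced.

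A reader might also infer that power is given away for nothing. That goes too far. Bonferroni has simple matching intervals, although none are planned here. Holm also uses more of the error allowance when some effects are null: with three real effects and one null at correlation 0, the family-wise error is 1.25% under Bonferroni and 4.0% under Holm, still within 5%.

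Nor does Holm rescue every p-value between 0.0125 and 0.05. A p-value of 0.04 passes only if the other three tests have all been rejected, and two tests at 0.03 both fail.

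Finally, the large gains require all four effects to equal f = 0.175. The article gives that value as the difference to be detected, not as the expected effect on every outcome at each time point, and it sets no rule that all four must succeed.

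**Conclusion.** The point holds as a cheap improvement, not as an error. On the article's only stated rule, the plan forgoes power on rejections after the first, while the chance of at least one rejection stays the same. The size depends on how many effects are real: roughly 5 to 10 points per test if all four are as planned, about 2 points if two are, and essentially none if one is. These figures rest on normal test statistics with the planned 80% power, two-sided tests, and correlations assumed between 0 and 0.9.

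That Holm never rejects less does not depend on the number of tests. This matters because the article does not say whether its four tests are two outcomes at two times or four scores (PA and the three PAHCO sub-competences); four scores at two times would make eight. The figures above are for four.

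**What to change.** State in Data analysis that the primary tests, listed by outcome and time point, are judged by the Holm step-down procedure at family-wise two-sided alpha 0.05. Under Sample size, keep 0.05/4 and describe it as the conservative basis of the calculation. Record the change before the statistician is unblinded.

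The cost is one sentence, with no change to participants, practices, data or the planned 567. The small downside is in reporting: intervals that match Holm decisions are less simple. Report Bonferroni-level intervals alongside, and note that they may include zero for some results that are significant under Holm.
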